**Microbiological testing for specific stool pathogens :** The collection and microbiological testing of random sample of 220 children at baseline and at first subsequent diarrheal episode is an essential component in this project. We have incorporated one reviewer's suggestion to repeat microbiological testing of stool specimen of the entire subsample at the mid-point of the project and will thus, be able; - i.) to assess the prevalence of asymptomatic bacterial, viral and parasitic infections at two different seasons, ii.) to describe the proportion of diarrhea attributable infection in the different treatment arms, and, iii.) to estimate the pathogen-specific attributable risk for diarrhea. In our pilot study in Mizque we successfully obtained stool samples of 80 children and completed microbiological testing in 74 (92.5%) of them. Protozoal and helminthic infections were recorded in 48.6% (36/74) (*G.lambli*a 33.8%, *E.hist/dispar* 23.0%). In 18 children (24.3%) a current diarrheal episode was reported. Bacterial infections were found in 5 children (*Salmonella* sp 2x, *Shigella* 1x, *E.coli* 2x). Infection status (protozoa and/or helminths) did not correlate with report of diarrheal illness (OR=0.3, CI-95%=0.08-1.1). In our trial, results from the individual stool investigations will be correlated with the data on symptoms from the health diaries and direct interviews and data on environmental and in-home water quality.

**Multiple transmission pathways and their effects on estimates of the preventable fraction:** The enteric pathogens that will be identified in this study can be transmitted to humans through multiple pathways (e.g., food, person to person, and water). These transmission pathways are interdependent. It is important to assess the impact of improving water quality through SODIS in the context of the multiple pathways of disease transmission. The data collected in this trial will allow us to examine the preventable fraction estimates due to SODIS use, by developing and analyzing mathematical models of disease transmission in the context of the 22 villages under study. Our group has extensive experience with such disease transmission models and will incorporate the field data into such a model. Several of our publications for such disease transmission models are included in the appendiceal material (Appendix G).

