(\* Note: the closest caretaker of the child will be contacted as respondent only if the team cannot locate the mother after two unsuccessful visits to the home)

Stool samples will be collected from a random sample of 220 children during the baseline morbidity surveys. The same children will be asked to provide two more samples at the time of their first symptomatic diarrheal episode and after 6 months follow-up. Testing of the stool specimen will be done at LABIMED, University of San Simon (UMSS)/Medical Faculty.

Systematic monitoring of the water quality of raw water sources used for drinking water and of household water samples after treatment with the SODIS device will be conducted. Testing for fecal coliform contamination will be done using portable equipment. More sophisticated analyses for bacteriophages and parasites (*Cryptosporidium* and *G. lamblia*) will be done at the laboratories of the Centro de Aguas y Saneamiento Ambiental/UMSS.

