Additionally, stool specimens will be collected from a random sample of 220 children during the baseline morbidity surveys. In each community specimens from two children for every one-year age group will be collected (ten total per village). We will obtain one stool specimen at baseline and after 6 months, and also one specimen at the onset of their first diarrheal episode and submit it for microbiologic analysis. Stool analysis at baseline and mid-term will allow us to estimate the pathogen-specific infection rates in asymptomatic cases in both intervention arms. Microbiologic testing of stools of the same cohort will be repeated at mid-point of the project to obtain a repeated measure of infection status (regardless of disease status) at another season. By conducting microbiologic testing of the subsequent 220 symptomatic diarrhea cases we will be able to obtain rates of pathogen-specific diarrheal illnesses and pathogens responsible for the differences in diarrheal illness between intervention and control group (see section D.6g. Specimen collection and testing).

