#### **D.6.g. Specimen collection and testing (stool and water specimens)**

An important component of our proposal is the collection and microbiological testing of stool specimen from study children. Data collection on pathogen-specific infections will be generated to elucidate three issues of particular interest in the current setting : i) the prevalence of asymptomatic bacterial, viral and parasitic infections in rural Bolivian children, ii) the proportion of diarrhea attributable to infection in the different treatment arms, and iii) the pathogen-specific attributable risk for diarrhea.

Prevalence of asymptomatic infection is obtained through the microbiologic testing of the random sample of 220 children at baseline. We will calculate the proportion of pathogen-positive stool samples among those children that were not classified as diarrhea. To obtain the proportion of diarrhea attributable to infection test results will be pooled from all symptomatic cases identified at baseline and at the time of their first episode. Since this will partly involve repeated measurements of the same individual we will account for the possible intra-person correlation by applying General Estimation Equation (GEE) approaches in the analysis (Zeger et al. 1988) (see also section D.9.). We will also explore how individual pathogen might be related to the probability of diarrhea.

These specimens will be tested for common causes of gastrointestinal illness due to viruses, bacteria and parasites. Stool specimens will be collected at baseline from a random sample of the children under five (N=220) and again at their first symptomatic episode later in the study. At the reviewers suggestion we will repeat testing the same cohort (regardless of disease status) at mid-point of the project. Field staff will distribute stool collection kits in the morning and collect them in the evening from the households if the child cannot produce a sample at the time of the visit. They will store the specimen in cooler boxes at 4 degrees C. and transport them to the local research office where refrigeration is possible. From there they are transferred to the central laboratory in Cochabamba within 48 hours. Participants will be notified by the study team about the test results and treatment initiated upon consultation with the medical center. A comprehensive array of tests will be performed at the Medical Faculty of the University of San Simon in Cochabamba.

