An important component of this research is the collection of microbiological testing of stool specimen from study children with appropriate consent. These specimen will be tested for common causes of gastrointestinal illness due to viruses, bacteria and parasites. Stool specimens will be collected at baseline from about 30% of the under five population (approx. 250 samples) in the participating villages and later during the study from about another 250 symptomatic cases with a diarrheal episodes. Field staff will distribute stool collection kits in the morning and collect them in the evening from the households if the child cannot produce a sample at the time of the visit. They will store the

specimen and transport them to the local research office from where they are transferred to the central laboratory (LABIMED) in Cochabamba. The nurse of the local health facility will be notified about the test results, and he/she will then contact the participant and initiate treatment upon a consultation at the health facility.

Water quality monitoring constitutes the second important component. Water samples of stored and SODIS-treated drinking water (in intervention arm) will be collected from about 10 households in every community (about 30% of the study sample) every two months. In addition samples of the raw water sources reported to supply the households with drinking water will be tested. All households will have consented to water quality monitoring of household drinking water.

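### The six-month stool round retests children already tested and referred for treatment, so it cannot give an unbiased second-season prevalence of persistent infection

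*Protocol*

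**What the plan says.** Protocol section D.1: "Stool samples will be collected from a random sample of 220 children during the baseline morbidity surveys". D.6.b gives the allocation: "In each community specimens from two children for every one-year age group will be collected (ten total per village"). Of later specimens D.1 says: "The same children will be asked to provide two more samples at the time of their first symptomatic diarrheal episode and after 6 months follow-up". D.6.g confirms that "we will repeat testing the same cohort (regardless of disease status) at mid-point of the project".

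The retest has a stated purpose. The Introduction to the revised application says it will allow the team "to assess the prevalence of asymptomatic bacterial, viral and parasitic infections at two different seasons". D.6.b says testing is "repeated at mid-point of the project to obtain a repeated measure of infection status (regardless of disease status) at another season", and also uses the mid-term stools for asymptomatic infection rates in both arms.

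Results do not stay in the laboratory. D.6.g: "Participants will be notified by the study team about the test results and treatment initiated upon consultation with the medical center". E.5 has the local health-facility nurse informed, after which "he/she will then contact the participant and initiate treatment upon a consultation at the health facility". Neither section limits this to children with symptoms or places it after the six-month specimen. D.11 adds that care comes from the regular health system, not the project team.

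For analysis, D.6.g pools symptomatic stools from baseline and first episode and uses GEE for correlation within a child. D.9 regresses diarrheal status of the specimen on pathogen presence, also by GEE.

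**The concern.** Testing at baseline identifies the positive children and sends them towards treatment, and the same children are then measured again. For an infection that would otherwise have lasted, the second measurement reflects what was done about the first. No group untested until six months is planned, and GEE for within-child correlation corrects standard errors without separating treatment from season.

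Two secondary results are at stake. The six-month prevalence would be read as the villages' prevalence in another season when it is biased downward for persistent parasites. The pathogen-diarrhea analysis, which serves the second specific aim, compares stools taken before any treatment with stools taken after it.

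**Working it through.** **Inputs from the protocol.** The subsample reproduces: 22 villages x 5 one-year age groups x 2 children = 220, and 220/660 = 33.3%. Pilot prevalence of any protozoal or helminth infection (C.1) is 36/74 = 48.6%, or about 220 x 0.486 = 107 positive children.

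**Assumed inputs.** The share of positives treated and cleared (f) and the share of those reinfected by six months (r) are not in the protocol.

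**Fall due to treatment alone, with no true seasonal change:** 48.6% x f x (1 - r).

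| f | r | Calculation | Fall | Six-month prevalence |
|---|---|---|---|---|
| 0.50 | 0.80 | 0.486 x 0.50 x 0.20 | 4.9 points | 43.7% |
| 0.80 | 0.50 | 0.486 x 0.80 x 0.50 | 19.4 points | 29.2% |
| 0.90 | 0.30 | 0.486 x 0.90 x 0.70 | 30.6 points | 18.0% |

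**Scale.** Treating the rounds as independent samples of 220 and ignoring clustering, the 95% half-width of a difference is 1.96 x sqrt(2 x 0.486 x 0.514 / 220) = 9.3 points. The middle and high cases would look like a clear change; the low case would not.

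**Other differences between rounds.** Children are six months older. In the pilot, any parasitic infection rose from 11.1% at 0-11 months to 86.7% at 24-35 months, so ageing pushes prevalence up in the youngest. D.6.b starts SODIS in intervention villages after the baseline survey. The net change therefore has no single cause, and its direction cannot be predicted.

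**Pathogen-diarrhea regression.** First-episode stools follow any treatment; baseline non-diarrheal stools precede it. Take the middle case, no true association, all diarrheal stools from the first episode and all comparison stools from baseline. The odds ratio is (0.292/0.708) / (0.486/0.514) = 0.44, falsely protective. This is an extreme illustration: diarrheal stools from baseline, or comparison stools from six months, would pull it towards 1.

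**Sections D and E side by side.** D.1, D.5, D.6.b and D.6.g include a six-month specimen. E.1 asks for one further sample, at a diarrheal illness. E.5 describes about 250 baseline samples and about another 250 from symptomatic cases, with no six-month round. D.6.g has the study team notify participants; E.5 has the nurse do so.

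**The case against.** The strongest defence is that the seasonal wording is descriptive. No section tests the baseline to six-month change, and D.6.g takes asymptomatic prevalence from baseline alone, which treatment cannot affect. That stands, but a descriptive six-month prevalence is still biased for persistent infections.

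Second, treatment depends on a consultation, and the protocol does not say how many positive children attend. E.5 belongs to a section without a six-month round. This makes the size uncertain and the low end modest. It does not remove the problem, because D.6.g describes both the retest and the treatment.

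Third, adjustment might be left to a statistical analysis plan that is not shown. Adjustment needs treatment to be recorded, however, and no analysis can supply specimens from previously untested children if none were taken.

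A reader might also infer that treatment shrinks the difference between arms at six months. The documents do not support that. SODIS starts after baseline, so baseline infections (prevalence p) are equal in expectation across arms. In a simple model of persistent infection without natural clearance, with share c cleared by treatment after baseline and acquisition risks a0 and a1 in the control and intervention arms, the arm difference is (1 - p)(a0 - a1) without treatment and (1 - p + pc)(a0 - a1) with it. At p = 0.486 and c = 0.8 the multiplier rises from 0.51 to 0.90, so the contrast widens. Both arms are also tested alike.

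Nor is a full second draw of two children per one-year age group workable: with the baseline draw it needs four per group per village. Pilot ages scaled to 30 children give 30 x 13/140 = 2.8 at 36-47 months and 30 x 8/140 = 1.7 at 48-60 months.

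**Conclusion.** The point holds for secondary stool results only. The six-month round does not give an unbiased asymptomatic prevalence for another season where infections persist. Treatment alone would lower parasite prevalence by about 5 to 31 points, given the pilot's 48.6%, assumed clearance of 50-90% and assumed reinfection of 30-80%. For short viral or bacterial infections the effect should be small. The pathogen-diarrhea association can be understated for persistent parasites, by an amount that depends on which stools are pooled.

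Baseline prevalence is unaffected. So is the primary outcome, which comes from diaries and weekly visits rather than stool results. It would be wrong to conclude that the project itself treats the children: it triggers referral, and the health facility delivers care. The change is worth making because it is cheap and prevents a misleading secondary result.

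**What to change.** Leave result notification and clinical care as they are.

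1. At the existing weekly visits, record any treatment given after each stool result. Cost: a few questions for 220 children, if the forms do not already ask.
2. Report six-month prevalence by prior result and treatment, adjusted for age. Include prior treatment and sampling round in the pathogen-diarrhea GEE.
3. Do not present the baseline to six-month change as seasonal. Confine any seasonal reading to control villages, which removes SODIS but not treatment or ageing. With 110 children per round, the half-width on the same basis becomes 9.3 x sqrt(2) = about 13 points.
4. If an unbiased second-season prevalence is wanted, take some or all six-month specimens from enrolled children not sampled at baseline, and age-standardise instead of filling every age stratum. The number of tests need not rise, and consent under E.1 already covers stool collection. The cost is losing some within-child repeats, which D.6.b wants.
5. Reconcile Sections D and E on the six-month specimen, the specimen numbers and who notifies participants of results.

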## D.7. Confounding factors

We will measure potential confounding factors. At the reviewers' suggestion we now include monitoring village characteristics that could relate to compliance such as measures of community coherence (collective projects, community bank accounts), peoples' attitudes and opinion about SODIS and motivations for its use. Additionally, we will monitor factors that might affect the diarrheal outcomes including secular trends beyond seasonal changes such as diarrheal disease epidemics in the area or any intervention-like activity in the area, regional or national level (such as media educational campaigns).

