Study design and the potential for confounding : For the control of confounding, we apply randomization at all levels (for the selection of villages and participants and for the allocation of the intervention). Additionally, we have matched villages on the pre-intervention outcome (diarrhea rate) as suggested by one of the reviewers. These two strategies (randomization and matching) are the most effective ways to reduce the variance of our effect estimate and to remove the potential bias due to confounding. In studying the effect of our intervention, confounding could result, as noted by the reviewer, if we differentially assigned treatment to those villages with either higher or lower inherent rates of diarrhea. However, by matching the villages on the baseline incidence of diarrhea the potential for confounding by differential initial conditions is greatly reduced. In further response to the reviewer, we now will further reduce the potential for mismatching villages by matching them on the basis of an estimate of diarrhea rates for eight weeks (previously based on a single 7 day recall diary) (Section D.6.b.). We will apply our newly adapted and pretested daily morbidity diaries combined with weekly home visits. This will reduce any misclassification bias in the pairing of villages prior to random assignment of the intervention. Based on our own experience in Bangladesh and Bolivia (Appendix F and F2) and that of others (Samanta and Van Wijk 1998), we will assess village characteristics that could be related to compliance by recording factors such as existing collective community efforts (e.g. commitments to community development, income generating projects, community banking accounts, cultural factors), to adjust for them in the analysis stage.

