## D.9. Data management and statistical analysis

Descriptive data analysis will be performed and selected demographic and environmental characteristics such age, sex, tribe/religion, household size, socio-economic/educational status, and the availability of water sources will be presented to indicate the effects of randomization and comparability of the intervention groups.

Comparison of rates: Cluster level incidence rates are used as the unit of analysis to compare incidence rates between intervention and control groups. Given the cluster size exceeding  $N=10$  Pearson  $\chi^2$  test can be used to compare cluster or group level incidence rates (Donner and Klar 1994). The calculations of Pearson  $\chi^2$  accounts for the degree of intracluster correlation and the variance inflation due to clustering (Klar et al. 1995).

Bias and Confounding: Randomization procedures throughout the hierarchical structure of this cluster-randomized trial should make intervention groups comparable at baseline at cluster- and village level. Any bias resulting from incomplete randomization or from monitoring specific village factors that relate to compliance as well as unpredictable outside factors (e.g. media) will be dealt with in the analysis.

Evaluation of effect modification will be achieved by including multiplicative interaction terms in a generalization of Poisson regression analysis adapted for the residual correlation of the total number of diarrheal episodes among children in the same cluster (see details below). The effects of well known factors that act as effect modifier such as the presence /absence of sanitary facilities in the compound, or previous exposure to health education will be considered. Preliminary assessment of interaction will be done by stratification and decision will subsequently be made whether to include interaction terms as indicators in the Poisson regression analysis.

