Multivariate statistics: Simple comparisons of rates will be done using software that is designed to accommodate the complexity of a cluster randomization design (SUDAAN). Simple Poisson regression cannot be used to make inferences about the effect of treatment in cluster randomization trials since it is constructed on the assumption that the conditional responses of individuals are statistically independent. An extension of the Poisson regression, generalized estimation equation approach (GEE) will be employed (Liang and Zeger 1986). For these regressions, the number of episodes of diarrhea for each child will be the outcome and, although we will report the inference based on robust estimates of the variance, we will assume the correlation within a cluster to be compound symmetry in the estimation procedure. We can possibly reduce the variance of the estimate of the treatment effect by adjusting for both baseline risk factors measured at either cluster level (cluster size, SES) or individual level (e.g. age, sex) (Klar et al. 1995). This becomes particularly important if the distribution of these covariates, by bad luck, are not similarly distributed in the treatment and the control arms of the study. We will also explore the strength of possible effect modification by looking at the inference of multiplicative interaction terms discussed above. We will account for the fact that some children will have different total time at risk due to our definition of an episode discussed in Section D.3 by including an offset term in the regression models that is the natural log of the total time (in days) that a child was at risk of diarrhea. Finally, the regression model will return parameters that can be interpreted as the marginal ratio of diarrhea rates relative to the variable of interest. Specifically, the models will return an estimate of the ratio of diarrhea rates in populations that have the treatment versus those with the controls, all other factors (covariates) being equal in the two populations. If we find significant effect modification with treatment, then the model will return rate ratios specific to levels of the interacting variable(s), e.g., the ratio of rates in treatment versus control among populations with unsanitary facilities.

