Sample size: Given the relatively large size of the study with 22 clusters and given that randomization will be employed at all levels we hope that residual bias will be measurable. While randomization of even small numbers of villages to intervention and non-intervention group ensures equal probability of assignment for each group, it cannot ensure that all potential sources of bias will be equally distributed. Pending our baseline field work in the trial villages, we have to anticipate a heterogeneity of the occurrence of baseline diarrheal diseases (our outcome) among the different village-clusters. A simple random assignment to the intervention or control group is unreliable to achieve baseline comparability among the study conditions. This applies particularly if the number of clusters in each condition is relatively small, as is in our study (N=11 villages). We thus, employ an *a priori* matching of the villages according to the baseline incidence of childhood diarrheal illness before random assignment of the intervention to one of the pairs.

Diarrheal episodes as outcome measure: Our outcome measure (diarrheal episodes) is subject to the influence of numerous measurable and unknown factors particularly in developing countries. By incorporating the suggestion made in the earlier review for *a priori* matching on the endpoint (baseline incidence of diarrhea) we have attempted to control for the effects of a number of unknown confounding factors as well as some of the factors that are difficult to assess such transient risk factors. We will be able to adjust for any relevant confounding factors that might randomly differ significantly in the groups.

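### D.7 lists attitudes to SODIS and motives for using it as confounders, and no rule confines adjustment to pre-allocation values; adjusting for them could bias the effectiveness estimate

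*Protocol*

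**What the plan says.** Four places in the protocol bear on this.

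- **D.7, Confounding factors.** It opens "We will measure potential confounding factors" and continues "we now include monitoring village characteristics that could relate to compliance such as measures of community coherence". The same list includes "peoples' attitudes and opinion about SODIS and motivations for its use". D.7 speaks of measuring and monitoring; it does not itself say what the analysis will do with these variables.
- **Introduction to the revised application, paragraph on study design and confounding.** Here "we will assess village characteristics that could be related to compliance by recording factors such as existing collective community efforts", and the stated purpose is "to adjust for them in the analysis stage". The examples given there are community development commitments, income-generating projects, community bank accounts and cultural factors.
- **D.9, Bias and Confounding and Multivariate statistics.** Bias from incomplete randomisation, or from "monitoring specific village factors that relate to compliance as well as unpredictable outside factors (e.g. media) will be dealt with in the analysis". The regression paragraph that follows describes the Poisson GEE model and names only baseline risk factors: cluster size and SES at cluster level, age and sex at individual level.
- **D.10, paragraph on diarrhoeal episodes as the outcome.** "We will be able to adjust for any relevant confounding factors that might randomly differ significantly in the groups".

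No section says that compliance-related factors must be measured before allocation in order to be used for adjustment.

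**The concern.** In a randomised comparison, a confounder is a pre-allocation variable that happens to be unevenly distributed between arms. A variable that changes because of the allocation is part of how the intervention works. The Project Summary says the trial is to estimate how much of the efficacy of SODIS survives as effectiveness under programme conditions. The introduction faults the earlier Kenyan trials because cultural norms there forced adherence. Willingness to use SODIS is therefore part of the effect being sought. Holding motivation constant between arms answers a different question and can hide a real benefit.

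There is also a precision cost. A score for wanting to use SODIS would be expected to separate the arms sharply, because control villages have no programme during follow-up. Such a covariate competes with the treatment term in a model with only 22 villages.

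**Working it through.** **Step 1: which variables are marked for adjustment.** D.7 and the introduction describe the same class, village characteristics connected with compliance. D.7 puts attitudes and motivation in that class. The introduction attaches adjustment to the class. D.9 repeats that bias connected with the class will be handled in the analysis. Read together, attitudes and motivation fall within what may be adjusted for, although no single sentence says so.

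**Step 2: when these variables arise.** D.6.b says the implementing agency starts in intervention villages after the baseline survey. D.1 and E.1 say control villages receive SODIS at the end of the trial. The introduction's paragraph on compliance says motives are explored among users and defaulters, groups that exist only once SODIS is in the village. Motivation for use is thus post-allocation and arm-dependent. Attitudes are too when measured after introduction.

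**Step 3: the plan's own design figure.** The D.8 formula is c = 2 + (z_α/2 + z_β)² × {(R0 + R1)/y + k²(R0² + R1²)} / (R0 − R1)². D.8 gives R0 = 5, R1 = 3.333, y = 10, k = 0.2, z values 1.96 and 0.84:

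c = 2 + 7.84 × (0.833 + 1.444)/2.778 = 2 + 6.43 = 8.43, rounded up to 9 per arm. This matches the protocol, which then raises it to 11.

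With c = 11, y = 30 and k = 0.2, solving for R1 gives about 3.73: 7.84 × (0.291 + 1.557)/1.613 = 8.98, against the required 9. The smallest reduction detectable with 80% power is about 25.4%, a rate ratio near 0.75. This applies to the comparison without such a covariate.

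**Step 4: illustration of bias.** The documents do not give the share s of the log effect that runs through these variables, so it is assumed over its whole range. The expected adjusted ratio is (2/3)^(1 − s). A simulation used 11 villages per arm, 30 person-years each, a log-scale village SD of 0.2 and 600 runs per row, and ignored pairing. The village score was assumed to differ by 0.6 between arms, with SD 0.15.

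| Share s | Expected adjusted ratio | Simulated adjusted ratio | Power, adjusted |
|---|---|---|---|
| 0% | 0.67 | 0.66 | 42% |
| 25% | 0.74 | 0.73 | 27% |
| 50% | 0.82 | 0.81 | 16% |
| 75% | 0.90 | 0.90 | 7% |
| 100% | 1.00 | 1.00 | 5% |

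The unadjusted ratio stayed at about 0.67 in every row, with power of 94% to 99%.

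**Step 5: precision.** The standard error of the log ratio rose from about 0.09–0.10 to about 0.22–0.23. Most of this follows from collinearity. The between-arm variance of the assumed score is 0.6²/4 = 0.09 and the within-arm variance is 0.15² = 0.0225, so the variance inflation is about (0.09 + 0.0225)/0.0225 = 5 and the standard error grows by about √5 = 2.2. This is why power falls even in the 0% row, where there is no bias. A score that separates the arms less would cost less.

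**Step 6: the D.10 sentence.** With 11 villages per arm, and ignoring pairing, a village-level covariate is significant at 5% only if the arms differ by about 2.086 × √(2/11) = 0.89 SD. Significance is thus a poor guide to which covariates matter: a prognostic imbalance below that size is passed over, while a chance difference in an unimportant variable can qualify.

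**The case against.** The strongest reply is that the protocol never says it will adjust for attitudes or motivation. D.7 only measures them. The introduction's adjustment sentence has pre-existing community traits as its examples, and attitudes are not among them. The D.9 sentence concerns bias that will be dealt with; it does not name covariates. The model paragraph lists baseline factors only, and a full covariate list is commonly left to the statistical analysis plan. All of this stands. A reader might infer that the protocol commits to an adjustment that would remove part of the effect; the documents do not support that.

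Nor are all these variables necessarily consequences of allocation. E.3 and E.9 say communities were contacted and had agreed to SODIS before the trial, D.11 says control villages know their delayed status, and C.3 mentions existing radio and educational material. Some attitudes could be recorded in both arms before allocation. Community coherence, also in D.7, can be a baseline trait. Adjusting for such baseline values is legitimate.

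Motives are already studied in the process evaluation, and D.7 does not list observed use, so nothing suggests that use itself would be a covariate.

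On D.10, a reader might infer that the sentence invalidates the 5% error rate. It does not. It states a capability in a limitations section and is restricted to relevant factors, and D.9 also plans a cluster-level comparison with no covariates named.

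What survives is that attitudes and motivation are classed as confounders, the class is tied to adjustment elsewhere, and the baseline list in D.9 neither claims to be complete nor withdraws the other statements.

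**Conclusion.** The point holds as a conditional one. The protocol leaves room for two different adjusted analyses: one confined to baseline covariates, and one that admits compliance-related factors whenever measured. The second could bias the effectiveness estimate, usually toward no effect, and widen its interval. Conditioning on a post-allocation variable can also bring in unmeasured causes of both motivation and diarrhoea, so the direction is likely but not certain.

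The size cannot be derived from the documents. The ratios of 0.74, 0.82 and 0.90 rest wholly on assumed shares of 25%, 50% and 75%, and the power losses rest further on an assumed score. At the 25% share the ratio of 0.74 still lies just beyond the 0.75 threshold from D.8, so bias alone would carry the estimate past that threshold only at larger shares. D.10 is a secondary matter: it leaves covariate choice open to observed differences in an unblinded trial. The point warrants a wording change; it is not a fault in the design.

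**What to change.** 1. In the introduction, D.7 and D.9, state that the effect estimate is adjusted only for prespecified covariates measured before allocation, for example the eight-week baseline village rate, age, sex, and community coherence if recorded at baseline.
2. In D.7, separate baseline village traits from attitudes, motivation and compliance observed after SODIS is introduced. Assign the latter to the process evaluation under the third specific aim (use and acceptance), or to a secondary analysis labelled as such.
3. In D.10, replace the sentence on factors that differ significantly by chance with a reference to the same prespecified list.

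The cost is wording only. Everything now planned is still collected, and the sample size and visit schedule do not change.
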